### Sample size

2.4

This study adopts a randomized, controlled, double-blind clinical trial design. Based on data from the study by Johnson et al,^[18]^ where withdrawal rate was 54.5% in the treatment group and16.7% in the control group, with an alpha of 5%, and a power of 90%, the estimated sample size for the 2 groups was 68 patients using the PASS 15 software (34 patients in each group). With an estimated dropout rate of 20%, a total number of 82 patients (41 patients in each arm) will be needed.

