### Outcome measures

3.2

Primary outcomes: The primary outcomes are the changes in the average daily alcohol consumption of the 2 groups before and after treatment and comparison of the scores of the psychological craving self-rating scale during the courses of treatment of 2 groups.

Secondary outcomes: The secondary outcomes include abstinence rates of the 2 groups during the follow-up period, days without consumption, and changes of Short Form Health Survey (SF-36) scores in 2 groups before and after therapy.

The researchers will use weekly self-reports during the follow-up period, clinicians’ judgments, and biochemical examinations to determine whether the patient is abstinent. If the patient has drunk no more than 1 cup since the last visit, the GGT level is normal, or has not increased since the last examination, and the respiratory alcohol concentration is less than 0.10 g/L, the patient is judged to abstain from alcohol.

From the first week to the sixth week, vital signs will be monitored daily. The physical examination will be carried out weekly. The respiratory alcohol concentration will be measured once a week, and drinking craving and adverse events will be evaluated weekly at the time of enrollment and at weeks 2, 4, 6, and 7, serum γ-glutamyl transpeptidase (γ-GT) and blood alcohol concentration will be detected. At weeks 0, 3, and 6, the doctors will give the patients electrocardiograms, and urine pregnancy, blood routine and blood biochemical levels will be detected. During the follow-up period, serum γ-GT and respiratory alcohol concentration will be measured once a week.

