### Statistical analysis

3.8

Data analysis will be performed using the SPSS 18.0 statistical software package. Categorical variables will be compared by use of chi-square analysis. Continuous variables between groups will be analyzed by independent sample *T* test. The repeated measure of analysis of variance (ANOVA) will be used to analyze the differences in the group. For all reported values will be expressed as mean ± SEM. The log-rank test will be applied to compare the cumulative probability functions. The Cox proportional hazards model will be applied to assess the hazard ratio of achieving 12 weeks of abstinence and the Kaplan–Meier method will be used to calculate the cumulative probability function of reaching 12 weeks of abstinence. The changes of desire measured by PACS will be compared at baseline and at week 6 through the *T* test. The changes of desire and resistance during the study will be analyzed by using mixed linear regression analysis. All statistical tests will be two-sided tests, and *P* < .05 indicates that the difference is statistically significant.

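### The 90% power in section 2.4 is calculated for an undefined binary rate and is not established for either of the two continuous primary outcomes

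*Protocol article*

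**What the plan says.** Section 2.4 (Sample size) takes its planning figures from a cited earlier study: "withdrawal rate was 54.5% in the treatment group and16.7% in the control group, with an alpha of 5%, and a power of 90"%. From these, "the estimated sample size for the 2 groups was 68 patients using the PASS 15 software (34 patients in each group"). A 20% dropout allowance raises the total to 82, or 41 per arm. The section does not define the withdrawal rate or give its time point. It names no outcome of the present trial to which the calculation applies.

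Section 3.2 (Outcome measures) names two primary outcomes. On the first it says "The primary outcomes are the changes in the average daily alcohol consumption of the 2 groups before and after treatment"; the second is a between-group comparison of craving self-rating scores during treatment. It then says "The secondary outcomes include abstinence rates of the 2 groups during the follow-up period", along with days without consumption and SF-36 change. The abstract gives the same split.

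Section 3.8 (Statistical analysis) plans chi-square tests for categorical variables and independent-sample t tests for continuous ones. Craving on the PACS is compared at baseline and week 6 by t test, and craving over the study is analysed by mixed linear regression. It adds that "All statistical tests will be two-sided tests", at the 5% level.

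**The concern.** A power figure belongs to one outcome, one assumed effect and one test. Here the outcome behind the figure is binary, while both outcomes on which the trial will be judged are continuous. Nothing in section 2.4 converts a 37.8-point difference in a rate (54.5 − 16.7) into a difference in daily consumption or in craving score.

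A reader of section 2.4 will take 82 patients as giving 90% power for the primary question, and nothing in the article supports that. If the effects on consumption and craving are moderate, the trial could easily miss them. A non-significant primary result would then be read against a power figure that was never worked out for it.

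**Working it through.** **Inputs.** From section 2.4: p1 = 0.545, p2 = 0.167, alpha 0.05, power 0.90, 34 evaluable per group, 20% dropout, 41 per arm. From section 3.8: two-sided tests, and a t test for continuous variables. Allocation is 1:1 (sections 2.1 and 3.1). No difference or SD is given for either primary outcome, so every standardized difference d below is an assumption.

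**Step 1: reproduce the stated sample size as a two-proportion result.** The mean rate is (0.545 + 0.167)/2 = 0.356, and (1.960 + 1.282)² = 10.507. With the pooled variance under both hypotheses:

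n per group = 10.507 × 2 × 0.356 × 0.644 / 0.378² = 10.507 × 0.4585 / 0.1429 = 33.7, rounded up to 34.

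The unpooled formula with continuity correction gives 33.5, also 34. Other standard variants give 29 (unpooled), 32 (pooled under the null hypothesis only) and 37 (the latter with continuity correction). The stated 34 per group is therefore reproduced as a comparison of two proportions, and 68 × 1.2 = 81.6 gives the 82. The 90% belongs to that binary comparison.

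**Step 2: what 34 per group gives for a continuous outcome.** For a two-sample t test with n per arm, power is the probability that a noncentral t variable with 2n − 2 degrees of freedom and noncentrality d × √(n/2) exceeds the critical value. With n = 34 there are 66 degrees of freedom, the two-sided 5% critical value is 1.997, and √17 = 4.123.

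| Assumed d | Noncentrality | Power, 34 per arm |
|---|---|---|
| 0.3 | 1.24 | 23% |
| 0.5 | 2.06 | 53% |
| 0.7 | 2.89 | 81% |
| 0.8 | 3.30 | 90% |

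Solving for d gives 0.80 (0.798) for 90% power and 0.69 (0.690) for 80%.

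**Step 3: how far this depends on dropout.** If all 41 per arm were evaluable, 90% power would still need d of about 0.73, and power at d = 0.5 would be 61%.

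**Step 4: sample size implied by a moderate effect.** If d were 0.5, 90% power would need 86 evaluable per arm, about 2.5 times the planned 34 (86/34 = 2.53). This only shows sensitivity to the assumption; the documents do not say that d is 0.5.

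**The case against.** Four objections deserve an answer.

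*The power for the primary outcomes could still be 90%.* This stands. A reader might infer that neither primary outcome has the stated power, but the documents do not support that. With no difference or SD, the power is unknown, not shown to be below 90%. The planning effect is itself very large: 54.5% versus 16.7% is an arcsine effect size of 0.82. If an effect of that size carried over to a continuous primary outcome, 34 per arm would give slightly more than 90% power. The protocol does not make that assumption, so this shows what is possible and does not justify the figure.

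*The t test is only part of the planned analysis.* This stands for craving. Section 3.8 also plans mixed linear regression of craving over the study, and power under that model may differ from the figures above. A reader might also want the alpha halved for two primary outcomes. Section 3.8 plans no such split, so the figures here use 5%.

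*The withdrawal rate is undefined.* This stands, and it limits what can be said. A reader might infer that the 90% belongs to this trial's follow-up abstinence outcome. That is plausible, because the rate is higher on treatment and is used as the benefit to be detected. However, section 3.2 defines abstinence by a composite of reported drinking, GGT and breath alcohol, and nothing shows that the planning rate has the same definition or time point. Under any reading it is a proportion, and neither primary outcome is.

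*The trial is a pilot, or an unseen document covers this.* Neither removes the point. The introduction uses the word pilot to justify six weeks of treatment, and in the same sentence says the aim is to assess efficacy. The problem is not an omission: the article states a power figure and its basis, and that basis does not match the primary outcomes it states.

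**Conclusion.** The point holds in this form: the stated 90% power comes from a two-proportion calculation and is not established for either primary outcome.

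The mismatch and the reproduction of 34 per group rest on the document alone. The size of the consequence rests on assumed standardized differences. Under a two-sided 5% t test with 34 evaluable per arm, the trial reaches 90% power only if d is about 0.80 or more, and power is close to one half at d = 0.5. The documents do not say which value is realistic, so they do not show that the trial is underpowered. It still needs correcting, because the power statement supports the reading of the primary result and changing it requires no more patients.

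**What to change.** Keep 82 patients and restate section 2.4 as follows:

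- Define the withdrawal rate: what event it counts and at what time point.
- State that the 90% power applies to that binary rate and not to the primary outcomes.
- For each primary outcome, give the difference detectable with 34 evaluable per arm under a two-sided 5% t test: d = 0.80 at 90% power and 0.69 at 80%. Translate these into units of daily consumption and PACS points using a stated SD and its source. The detectable difference is d × SD.
- Note that the craving figure refers to the t test, and that the repeated-measures model may give a different one.

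The cost is that the stated power for the primary outcomes becomes less favourable.

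A reader might see promoting abstinence to sole primary outcome as the simpler repair. It is not recommended. It would assume that the planning rate matches this trial's abstinence definition, which is unverified, and it would take consumption and craving out of the primary question. It would also be a protocol modification needing ethics approval and a registry update under section 2.2, so more than a change of wording.

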### Treatment plan

3.1

All patients will receive psychosocial alcohol treatment based on psychological education elements, motivational interviews, and cognitive behavioral therapy, including informing patients about the causes and consequences of alcohol dependence, the necessity of treatment, and how to conduct the treatment of alcohol abstinence. At the same time, family members should be educated about compliance with the treatment plans. Regular psychosocial alcohol treatment was given to abstainers once a week for 6 weeks. According to the abnormal blood chemical features of the patients, the patients will be selectively given corresponding treatment measures such as liver and kidney preservation, correction of electrolyte and acid–base disturbance, effective fluid infusion, vitamin supplementation, etc. The patients with severe withdrawal symptoms during abstinence could be treated with benzodiazepines.

Patients will be randomly assigned to receive ASF or placebo in a ratio of 1:1.

Experimental group (ASF group): On the basis of basic treatment, the patients will take 10 g ASF 3 times daily, dissolved in 150 mL of warm boiling water, for 6 weeks.

ASF used in this test is provided by the pharmaceutical Department of Affiliated Hospital of Chengdu University of Traditional Chinese Medicine (Sichuan, China).

The whole ingredients of ASF are Epimedium 15 g, Semen Ziziphi Spinosae 15 g. One dose every day, 10 g each time, 3 times a day. The herbs in ASF are mixed, processed, filtered, and spray-dried by pressure to form granules, and packaged into single-dose pouches, each weighing 10 g.

Control group: In addition to the basic treatment, the participants will take placebo granules of 10 g each time, 3 times a day. The placebo granules were dissolved in 150 mL of warm boiling water, for 6 weeks.

The placebos in the study are composed of starch and have no active ingredients.

By adding various food pigments, the appearance and taste of the placebo are as close to the real granules as possible.

The drug distribution of the study will be performed by a pharmacist who is not involved in clinical management to preserve the double-blind design. Each time the patient takes the medication, the research nurse will supervise the process and count the number of medication bags taken and not taken.

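### The 20% dropout allowance is computed as 68 × 1.2 rather than 68 / 0.8, so 82 patients leave about 65 at that dropout, not the 68 planned

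*Protocol article*

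**What the plan says.** Section 2.4 (Sample size) of the protocol article takes its planning rates from an earlier trial, "where withdrawal rate was 54.5% in the treatment group and16.7% in the control group", with 5% alpha and 90% power. From these it reports that "the estimated sample size for the 2 groups was 68 patients using the PASS 15 software (34 patients in each group". The next sentence adds the allowance for losses: "With an estimated dropout rate of 20%, a total number of 82 patients (41 patients in each arm) will be needed". Neither the test chosen in PASS nor the inflation formula is shown.

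Section 2.5 (Randomization and allocation concealment) repeats 41 per group, and section 3.1 (Treatment plan) confirms equal allocation: "Patients will be randomly assigned to receive ASF or placebo in a ratio of 1:1". Section 3.8 (Statistical analysis) gives chi-square analysis for categorical variables and says "All statistical tests will be two-sided tests".

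**The concern.** The section gives three figures that should fit together: a requirement of 68, an expected dropout of 20%, and an enrolment of 82. Taking 20% away from 82 should return at least 68, and it does not.

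This sentence is the article's only justification of the enrolment target. A reader, an ethics committee or the study team will take it to mean that one patient in five can be lost with the planned number still intact. The enrolment actually tolerates somewhat less than that.

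**Working it through.** **Inputs** (all from section 2.4 unless noted): base size 68 in total, 34 per group; dropout 20%; enrolment 82 in total, 41 per arm; rates 54.5% and 16.7%; alpha 5%; power 90%. Tests are two-sided (section 3.8) and allocation is 1:1 (section 3.1).

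**1. Reproducing the plan's 82.** Multiplying by (1 + dropout):
- total: 68 × 1.20 = 81.6, rounded up to 82
- per arm: 34 × 1.20 = 40.8, rounded up to 41

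Both stated figures are matched exactly. Dividing by (1 − dropout) does not give 82.

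**2. The allowance that keeps 68.**
- total: 68 / (1 − 0.20) = 85
- per arm: 34 / 0.80 = 42.5, rounded up to 43, so 86 with equal arms

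The enrolment of 82 is 3 short of 85 and 4 short of 86, which is more than rounding explains.

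**3. What 82 delivers.**
- at 20% dropout: 82 × 0.80 = 65.6 in total, or 41 × 0.80 = 32.8 per arm
- shortfall against 68: 68 − 65.6 = 2.4, so 2 to 3 patients
- largest dropout that still leaves 68: (82 − 68) / 82 = 14 / 82 = 17.1%

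**4. Effect on power.** This needs a test, and the article names none for the sample size. With p₁ = 0.545, p₂ = 0.167, difference d = 0.378 and V = p₁(1 − p₁) + p₂(1 − p₂) = 0.387, three candidates (two-sided 5%) give:

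| Method | 34 per arm | 33 per arm | 32 per arm |
|---|---|---|---|
| Uncorrected chi-square, exact power | 92.9% | 92.1% | 91.0% |
| Pooled z-test, normal approximation | 92.1% | 91.3% | 90.4% |
| Unpooled, continuity-corrected | 90.4% | 89.4% | 88.4% |

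The last row is Φ[(d − 1/n) / √(V/n) − 1.96]. At n = 32.8 it gives 89.2%, and the pooled z-test gives 91.1%.

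**5. Can the test behind 68 be identified?** Not from the article.
- The unpooled formula gives 28.5 per arm. With the continuity correction it becomes 33.5, rounded up to 34, which matches.
- A Freedman log-rank calculation that treats 54.5% and 16.7% as event-free proportions gives 44 events. The average event proportion is 1 − (0.545 + 0.167)/2 = 0.644, and 44 / 0.644 = 68.3, which is also consistent with 68.
- The pooled two-proportion formula gives 32 per arm (64 in total) without the correction and 37 per arm (74) with it. Neither total is 68.

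Two different methods therefore lead to about 68, and the article does not allow a choice between them.

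**The case against.** The strongest reply concerns the consequence, since the arithmetic is not open to dispute. A reader might infer that the trial loses its 90% power. The article does not support that. The only categorical test it names is chi-square, with no mention of a continuity correction, and by that test power stays at about 91–92% with 32 to 33 per arm. A drop to 88–89% appears only under a formula picked because it happens to return 34, and the log-rank route fits about as well. Fisher's exact test gives about 87% at 33 per arm, but it is already at 88% with 34, so the dropout arithmetic is not the cause there. This part of the reply stands.

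A second reply is that fewer patients may be lost than planned. Section 3.5 (Compliance) says patients who stop treatment will still be followed up under intention-to-treat unless they leave the study, and section 2.9 (Termination and withdrawal criteria) says data gathered before withdrawal are kept and used. That may soften the practical effect. It does not repair section 2.4, which makes its own allowance for losses and should compute it correctly.

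A third reply is that 20% was meant as a recruitment margin added on top. The text calls it an estimated dropout rate, and the usual meaning of that is a share of those enrolled. If a margin was intended, the sentence still misstates the dropout that 82 can absorb and needs the same correction.

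**Conclusion.** The point holds as an arithmetic error: 68, 20% and 82 do not fit together. At 20% dropout, 82 patients leave about 65, which is 2 to 3 below the plan's own 68, and 82 covers at most about 17% dropout. This rests on reading the dropout rate as a share of those enrolled and on taking 68 as given. That the authors multiplied by 1.2 is inferred from the exact match, since no formula is printed.

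The effect is small. Whether power at that number is above or below 90% depends on the unnamed test behind 68, so neither a loss of the planned power nor a need for more patients is established. The missing formula could be in a fuller protocol, but nothing there could make 80% of 82 equal 68.

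**What to change.** Keep the enrolment at 82 and correct the sentence in section 2.4. It should say that 82 patients (41 per arm) leave 68 at up to about 17% dropout, and about 65 at 20% dropout. Name the test used in PASS for the 68, and restate the power at about 65 patients for that same test. The figure of about 89% should not be written in unless PASS was in fact run with the unpooled, continuity-corrected method.

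If the sponsor prefers to keep 68 patients at a full 20% dropout, the matching enrolment is 85, or 86 with equal arms, and the 41 per group in section 2.5 would change with it. The finding does not require this.

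The cost of the recommended change is one sentence and one rerun in PASS. Design, randomisation and analysis stay as they are.

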### Randomization and allocation concealment

2.5

The statistical professionals will number the random numbers generated by SAS software, and number them according to the serial number. According to this randomization code, the random numbers will be divided into an experimental group and a control group. The randomization results will be included into the opaque envelope. The enrolled patients will open the envelopes according to the entry sequence and be randomly divided into 2 groups with 41 patients in each group using the random numbers generated by SAS software. At the same time, the drug package number is generated by computer according to the random number, and the pharmaceutical Department of Affiliated Hospital of Chengdu University of Traditional Chinese Medicine will be responsible for the preparation and packaging of drugs.

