### Blinding

2.6

In order to ensure the consistency of appearance, shape, smell, and specification, Chinese medicine and placebo will be produced, packaged and labeled by the pharmaceutical Department of Affiliated Hospital of Chengdu University of Traditional Chinese Medicine. The statistical professionals unrelated to this study will work out the procedures for designing, distributing, and breaking randomized code lists. The initial parameters about randomized code lists will be sealed in envelopes as confidential data. The emergency letter will be set up in each drug number, including the appropriate drug group. In case of clinical emergency, it can be opened to break randomized code lists. When randomization is broken, researchers, project leaders, and clinical inspectors will be required to participate in the process and record it in detail. Emergency letters will be uniformly recalled after the end of the test. Patients, investigators, and persons performing data analysis will remain blinded from the time of randomization to time of database unlock.

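### Section 2.5 has patients open envelopes holding the randomization results; read literally this shows them their group, which conflicts with the blinding in section 2.6, and nothing in the protocol resolves it

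*Protocol article*

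**What the plan says.** The allocation procedure is in section 2.5 (Randomization and allocation concealment). After the numbers are generated, "the random numbers will be divided into an experimental group and a control group". The text that follows gives the content of the envelope and who opens it: "The randomization results will be included into the opaque envelope. The enrolled patients will open the envelopes according to the entry sequence". The same sentence goes on to say that the patients are thereby divided at random into two groups of 41. The coded drug supply comes last, as a step alongside: "At the same time, the drug package number is generated by computer according to the random number".

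Section 2.6 (Blinding) describes the protection of the code. Statisticians unrelated to the study control the code lists, and the initial parameters of those lists are sealed as confidential. The group is written in a separate document: "The emergency letter will be set up in each drug number, including the appropriate drug group". That letter is for clinical emergencies, and opening it requires several named functions to take part and a detailed record. The section closes: "Patients, investigators, and persons performing data analysis will remain blinded from the time of randomization to time of database unlock".

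Section 2.1 calls the trial double-blind. Section 2.9 lists unblinding, without further definition, among the termination and withdrawal criteria.

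**The concern.** Sections 2.5 and 2.6 give conflicting accounts of what a patient may know at the moment of allocation. If staff follow section 2.5 in its ordinary sense, the patient opens a paper that shows the group. Anyone present at the opening could see it too, although the article does not say who is present.

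This matters because of the outcomes chosen. Section 3.2 (Outcome measures) makes change in average daily alcohol consumption and a craving self-rating the primary outcomes. Section 3.3 (Questionnaires) obtains consumption from a Timeline Follow Back completed with the patient from a weekly diary. Both therefore rest on what the patient reports. A patient who knows that he or she takes the herbal granules, or starch, may report drinking and craving differently for that reason alone. A difference between the groups could then not be attributed to ASF with confidence, and no analysis can restore the blind afterwards. Biochemical measures are collected (serum γ-GT, breath and blood alcohol), but neither primary outcome is defined by them.

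**Working it through.** No arithmetic decides this point. The check is to set the sentences side by side and test each possible content of the envelope against them.

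**Step 1: what the envelope holds.** The protocol does not define the randomization results. The sentence just before describes the division of the numbers into two named groups, so that division is the nearest thing the phrase can refer to. The sentence just after makes opening the envelope the act by which patients are divided into those groups. In ordinary usage, the envelope shows the group.

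**Step 2: whether the package number could be the content.** The package number appears only after the envelopes have been filled and opened, and is introduced as happening at the same time. It is a parallel step, and the text does not name it as the content of the envelope.

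**Step 3: each reading against the rest of the protocol.**

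| Text | Envelope names the group | Envelope holds only a number |
|---|---|---|
| 2.5, order of sentences | Fits | Needs a meaning that is not stated |
| 2.6, blinding from randomization | Contradicted | Fits |
| 2.6, emergency letters holding the group | Largely pointless, since the patient already knows | Fits |
| 2.1, double-blind | Contradicted | Fits |
| 3.1, independent pharmacist and matched placebo | Largely pointless | Fits |
| 3.5, follow-up interviewer blinded to allocation | At risk, since the patient could disclose the group | Fits |

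The local wording of section 2.5 favours the first reading. The rest of the protocol favours the second. No sentence settles the matter.

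**Step 4: what is exposed under each reading.** The planned sample is 2 × 41 = 82. If the envelope names the group, all 82 patients would learn it on entry and both primary outcomes would be affected. If it holds only a number, no patient is unblinded by it. The protocol gives no means of estimating the size of any reporting bias, so none is given here.

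**The case against.** The strongest reply is that section 2.5 nowhere says the envelope names the group. It speaks of random numbers, a randomization code and a package number derived from them, and an envelope holding a number fits that vocabulary. The safeguards elsewhere make little sense otherwise: witnessed emergency letters that are recalled at the end, code lists kept by outside statisticians, a pharmacist outside clinical care, a matched placebo and a blinded interviewer. On this view the article describes a coded-package, double-blind trial with one badly worded sentence, and a fuller protocol may contain the proper procedure.

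Most of this stands as evidence of intent, and it rules out a stronger claim that a reader might infer: that the trial is in effect open-label, that all 82 patients will be unblinded, and that all of them would then meet the unblinding criterion in section 2.9. Each of those statements holds only if the envelope names the group, which is not established. The criterion in section 2.9 is also a bare list item, and its natural counterpart is the emergency code break of section 2.6.

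The reply does not remove the conflict. The article has not left this step to another document: it states what goes into the envelope and who opens it, and that statement is at odds with section 2.6. If a code-only envelope was intended, the text still has to be changed, because it says something else.

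**Conclusion.** The conflict between sections 2.5 and 2.6 is real and unresolved in the document. On its ordinary reading section 2.5 discloses the group to the patient, whereas section 2.6 requires patients and investigators to remain blinded from randomization. A code-only envelope is a plausible intention, but it is not stated.

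The consequence is conditional. Under the literal reading, patient blinding is lost for the whole sample and both patient-reported primary outcomes are exposed. Under the code-only reading, the defect is confined to the wording. The documents do not support saying that patients will be unblinded, only that a site following section 2.5 as written could unblind them. The point deserves correction because the possible loss cannot be repaired at analysis and the remedy is very cheap.

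**What to change.** Amend section 2.5 so that it agrees with section 2.6:

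- The next eligible patient is allocated the next drug package number in sequence.
- Any envelope or other material seen by the patient or by site staff carries only that number and never the group. If envelopes are kept, state what they contain and who opens them.
- The code list linking numbers to groups stays with the unrelated statistician and the pharmacy.
- The sealed emergency letters of section 2.6 are the only documents at the site that reveal the group.

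If patients have already been allocated, record what their envelopes contained and who saw the contents, so that the state of the blind can be reported.

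The cost is a wording amendment, with the ethics approval and registry update that section 2.2 already requires for any modification. Numbered packages, emergency letters and an independent pharmacist are already planned, so no new staff or material is needed. The sample size and the analysis do not change.

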### Recruitment

2.3

The patients will be recruited from the outpatient or inpatient department of the Affiliated Hospital of Chengdu University of Traditional Chinese Medicine. The clinicians participating in the withdrawal treatment unit will conduct preliminary screening of patients in the inpatient or outpatient department, and briefly describe the study to the patients who meet the criteria. If the patients are interested in participating, the clinician will alert the research team. A member of the research team will provide them with a comprehensive oral and written description of the research's aims and procedures and the research team members will understand their rights and responsibilities while participating in the study. Screening examinations only be performed after they have agreed to participate and signed the informed consent form. During screening, the patients will undergo related examinations to make sure that all inclusion criteria and none of the exclusion criteria are met.

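### The trial mixes inpatients and outpatients, but the stated t and chi-square tests ignore setting; adding setting at enrolment to the analysis would protect precision at almost no cost

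*Protocol article*

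**What the plan says.** - **Population.** Section 2.3 (Recruitment): "The patients will be recruited from the outpatient or inpatient department" of a single hospital. The abstract also names both groups. The expected share of each is not given.
- **Allocation.** Section 2.5 (Randomization and allocation concealment) describes SAS random numbers in opaque envelopes, opened in the sequence in which patients enter. Patients are to "be randomly divided into 2 groups with 41 patients in each group using the random numbers generated by SAS software". No stratification factor is mentioned.
- **Analysis.** Section 3.8 (Statistical analysis): "Continuous variables between groups will be analyzed by independent sample" t test. Categorical variables go to chi-square, and the change in PACS craving score from baseline to week 6 also goes to a t test. Mixed linear regression (craving over time) and a Cox model (12-week abstinence) are named without covariates.
- **Data collected.** The demographics listed in section 3.3 (Questionnaires) are age, gender, marital status and occupation. Setting is not among them.

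**The concern.** Setting is known before randomisation. It could well predict drinking, because patients on a ward and patients at home plausibly differ in access to alcohol and in supervision. The first primary outcome is the change in average daily consumption, and days without consumption is a secondary outcome.

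If setting matters and is left out, two things follow. The inpatient share can differ between arms by chance, which moves the estimate in that one trial. Even with perfect balance, the difference between settings stays in the error variance and lowers power. In a trial of 82 both effects can be noticeable.

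**Working it through.** **The plan's own figure.** Section 2.4 gives 34 per arm from rates of 54.5% and 16.7%, "with an alpha of 5%, and a power of 90"%; section 3.8 says "All statistical tests will be two-sided tests". The two-sided pooled formula gives 32 per arm, and 37 with continuity correction. The stated 34 lies between them and has 92.1% power by normal approximation. The total of 82 is 68 × 1.2 = 81.6, rounded up. Setting plays no part in this calculation.

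**Inputs.** From the document: 82 patients, 41 per arm, two-sided 5% test, no setting term. Assumed, because the document gives neither: the inpatient share f (20% to 50%) and the setting gap D (0.5, 1.0 or 1.5 within-setting SD, on the scale of the analysed outcome).

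**Step 1: chance imbalance.** With K inpatients among 82 and 41 per arm, the number X in one arm is hypergeometric (82, K, 41). The difference in inpatient share is |X − (K − X)|/41.

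| Inpatients K (share) | ≥10 points | ≥15 points | ≥20 points |
|---|---|---|---|
| 16 (20%) | 16.2% | 4.9% | 1.1% |
| 25 (30%) | 33.7% | 14.9% | 5.4% |
| 41 (50%) | 37.7% | 18.5% | 7.7% |

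**Step 2: shift in the realised estimate.** Shift = imbalance × D.
- 10 points: 0.10 × 0.5 to 0.10 × 1.5 = 0.05 to 0.15 SD.
- 20 points: 0.20 × 0.5 to 0.20 × 1.5 = 0.10 to 0.30 SD.

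For scale, the effect detectable with 90% power at 34 per arm is (1.96 + 1.2816) × √(2/34) ≈ 0.79 SD.

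**Step 3: precision lost.** The share of variance due to setting is R² = f(1 − f)D² / (1 + f(1 − f)D²), and ignoring it multiplies the standard error by 1/√(1 − R²). For f = 0.5:
- D = 0.5: R² = 0.0625/1.0625 = 0.059, like losing 0.059 × 82 ≈ 5 patients.
- D = 1.0: R² = 0.25/1.25 = 0.20, standard error × 1.12, like losing about 16.
- D = 1.5: R² = 0.5625/1.5625 = 0.36, standard error × 1.25, like losing about 30.

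**Step 4: simulation of the test.** Normal outcome, 82 analysed, 40 of them inpatients (so that each stratum splits evenly), 10,000 runs per cell. The treatment effect is 0.72 SD, which has about 90% power at 41 per arm: 3.2416 × √(2/41) ≈ 0.72.

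| List / analysis | Power at D = 0.5 / 1.0 / 1.5 | Type I error at D = 0.5 / 1.0 / 1.5 |
|---|---|---|
| Unstratified, unadjusted | 87.1 / 81.8 / 73.0% | 5.3 / 5.1 / 5.2% |
| Stratified, unadjusted | 88.5 / 84.3 / 77.9% | 4.5 / 2.7 / 1.4% |
| Unstratified, adjusted | 88.9 / 89.1 / 89.4% | 4.9 / 4.8 / 4.8% |
| Stratified, adjusted | 89.4 / 89.3 / 89.7% | 5.0 / 4.9 / 5.1% |

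Adjustment recovers the power with either list. Stratifying without adjusting recovers little and makes the test conservative. These runs cover a continuous outcome only; nothing was computed for the abstinence rate.

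**The case against.** **The article is condensed.** It does not say that the list is unstratified. Section 2.6 (Blinding) keeps the parameters of the code lists sealed, and these could include blocks or strata. Covariates for the mixed and Cox models may sit in an unseen analysis plan. This stands in part. A reader might infer that no analysis at all accounts for setting, but the text supports this only for the t and chi-square tests, which have no place for a covariate. Likewise, envelopes opened in entry order and fixed only at 41 per arm point to a single list without proving it.

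**The setting gap may be small.** Sections 3.1, 3.2 and 3.5 describe nurse-supervised doses, daily vital signs, and records of hospitalisation and admission. If all patients are treated in hospital, the difference in access to alcohol largely disappears for the six weeks. This stands: the document does not say where outpatients are treated. Setting at enrolment could still mark differences at baseline and during follow-up.

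**The outcome is a change score.** A constant level difference between settings cancels in a change from baseline. This also stands. D must be read as a gap in change, and the document gives no basis for its size or direction.

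**Not stratifying 82 patients at one hospital is acceptable.** Agreed. The list is the lesser issue, as the simulation shows.

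**Conclusion.** The point holds as one of precision. The stated between-group tests leave out a plausible predictor that is known before randomisation. A 10-point imbalance in inpatient share would arise in about 16% to 38% of trials, while 20 points is uncommon (1% to 8%). The larger cost is power. With about half inpatients, the unadjusted test loses about 2, 7 or 16 percentage points (89% down to 87%, 82% or 73%) for gaps of 0.5, 1.0 or 1.5 SD.

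These sizes rest on an assumed inpatient share and setting gap, and on all 82 being analysed. If setting does not predict the outcome, nothing is lost.

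A reader might infer that the comparison is biased, or that an imbalance could not be told apart from an effect of ASF. Neither follows. Chance imbalance under valid randomisation is part of the error that the test already allows for (simulated type I error 5.1% to 5.3%), and if setting is recorded, an imbalance can be seen and adjusted for.

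**What to change.** 1. Record setting at enrolment (inpatient or outpatient) for every patient, and state where each group is treated during the six weeks.
2. For consumption, craving and SF-36, replace the unadjusted t tests with a linear model (ANCOVA or mixed model) that includes setting at enrolment.
3. For abstinence, use a Cochran-Mantel-Haenszel test stratified by setting in place of the plain chi-square, and stratify the log-rank test and the Cox model by setting.
4. Optional, and only if enrolment has not begun: generate the list separately for inpatients and outpatients in permuted blocks. Do this only together with items 2 and 3. If enrolment has begun, keep the existing list.

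Cost: one data field, a few lines of analysis text fixed before unblinding, and one degree of freedom in the linear models. If the list is stratified, it also needs new list and kit numbering, and the arm totals may differ slightly from 41/41.
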